## 8.5 Quantitative Analyses.

We will examine whether study randomization to the three intervention arms resulted in similar provider and patient groups by comparing patient and provider level demographics with descriptive statistics. Comparison of the primary outcome between arms will be conducted based on provider arm assignment, in accordance with intention to treat. We will use generalized linear mixed-effect models with logistic regression to examine the difference in PrEP uptake (primary outcome) across arms. To account for the relationship among primary outcomes for patients with the same provider, we will specify a random provider effect. In addition, because some patients may return over the study period and be assisted by a different provider than their initial visit, we will specify a random effect for each patient, and assume a joint multivariate normal distribution for these provider and patient random effects. We will adjust these comparisons for any demographic differences

observed between arms. We will examine the primary outcome stratified by race/ethnicity. In exploratory analyses, we will examine whether intervention effects attenuate over time, as providers and patients may become accustomed to the intervention. **Secondary Outcomes:** Similar to our methods for comparing the primary outcome between provider arms, we will also compare the rate of male partner HIV self-test completion (confirmed via text message or phone/video call) with generalized linear mixed-effect models with a provider and patient level random effects. We will use similar methods to compare the HIV test completion rates of male partner and patients who score low-risk. We will consider adjustment for factors that are imbalanced between arms in these analyses. In addition, we will also examine PrEP uptake among low-risk score patients to determine whether providers who are receiving the intervention are being influenced in their behavior more generally, or if the intervention effect is specific only to intervention patients. R (ver 4.1) will be used for analyses.

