Patients who score medium or high (4-10) will be assigned a study arm based on their provider's group. This will occur automatically via programming integrated into the EHR based on the provider and the type of scheduled visit. The score will be recorded in EHR but it will not be labeled, i.e. a number will be there but nothing about HIV or risk of HIV. This medium/high score group is whom we consider **PrEP-eligible** (e.g., *at substantial HIV risk*) and is the focus of this implementation science study. Based on our preliminary data, we anticipate that a minority of patients (5-10%) will fall into these categories of medium or high risk.

**Clinical trial arms.** The Interventions are guided by the Information-Motivation-Behavior model of behavior change (**Figure 1**).

-Arm 1 Control: standard of care

-Arm 2 Patient-level intervention: patients will be shown a 2.5-minute PrEP animation (information) and their personalized HIV risk messaging (motivation)

-Arm 3 Patient and Provider multi-level intervention: patients will be shown a 2.5-minute PrEP animation (information) and their personalized HIV risk messaging (motivation) AND providers will receive an EHR alert about their patient's personalized HIV risk messaging and a recommendation to offer PrEP. The alert will allow the provider to accept to add the required laboratory tests to start PrEP or decline altogether. Orders will have to be signed by providers but the correct laboratory tests will be ordered to save time and ensure accuracy.

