## 5. STUDY POPULATION

### 5.1 Selection of the Study Population

**Provider eligibility:** N=42 ObGyn providers will be randomized. We chose providers as the unit of randomization to minimize contamination of the arms as many providers see patients at more than one clinic site. This will reduce the provider from being exposed to both interventions and unconsciously applying them to patients in the control arm.

**Patient eligibility:** Cisgender women of the enrolled providers aged 15-65 years scheduled in Epic for one of the following visit types: well-woman exam (annual exam), STI testing, pre-conception counseling, or contraception consult (birth control) will complete the eSHxForm. Programming in Epic will assign each patient to a study arm based on their provider's assigned study group. The age range was selected based on the United States Preventive Services Task Force (USPSTF) HIV Testing Recommendations, and PrEP FDA-approved age of 15 years. Based on preliminary clinical data, we estimate that we will have 23,400 women who will complete the eSHxForm and an estimated 5% (n=1170) will fulfill eligibility for PrEP.

**Staff eligibility:** N= 50 clinical staff who work at one of the six Obgyn clinics. These will include front desk, medical assistants, nurses, and clinic managers.

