## **7.2 Cisgender Female and Transgender Male Patients**

7.2.1 All patients of providers who have the eligible visit types scheduled will be enrolled. We will request for them to complete the eSHxForm before arrival at the clinic or immediately before seeing a provider.

7.2.2 Waiver of informed consent is being requested (see below **Section 12.5.3**) for the eSHxForm and clinical trial procedures. Whereas a waiver of documentation of consent (e.g., oral consent) is being requested for in-depth interviews.

7.2.3 Semi-structured in-depth interviews to evaluate the project (e.g., mainly processes) will occur throughout the project until we obtain feedback from 10-12 patients from each HIV risk level (n=30-36, low, medium, and high). We are not interested in the patients themselves for this portion and will not collect any of their PHI as part of these in-depth interviews.

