## 8.4 Randomization and Blinding

ObGyn providers will be randomly assigned to one of three study arms based on minimization techniques developed by Pocock and Simon. This minimization approach reduces covariate imbalances by utilizing non-uniform assignment probabilities for the different arms. The study arms will be balanced over the different clinics with equal sampling rates. Providers will be randomized in equal proportions between arms (14 providers per arm). All study personnel, study analysts, and patients will be masked to group assignment. Providers will be unmasked to group assignment. New providers who join a practice after another provider has left will undergo randomization.

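### The primary model keeps return visits under a provider-based arm, so a woman already shown the Arm 2/3 content can later count as an Arm 1 record; a patient random effect does not remove that carry-over

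*Protocol*

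**What the plan says.** - **Enrolment is by visit.** Section 7.2: "All patients of providers who have the eligible visit types scheduled will be enrolled". Earlier participation is not among the exclusions for women in section 5.3.
- **Arm comes from the provider.** Section 4, on women who score medium or high: "This will occur automatically via programming integrated into the EHR based on the provider and the type of scheduled visit". Section 5.1: "Programming in Epic will assign each patient to a study arm based on their provider's assigned study group".
- **The primary comparison follows the provider's arm.** Section 8.5: "Comparison of the primary outcome between arms will be conducted based on provider arm assignment, in accordance with intention to treat".
- **Returns to another provider are expected.** Section 8.5 foresees that "some patients may return over the study period and be assisted by a different provider than their initial visit". Its whole response is: "we will specify a random effect for each patient, and assume a joint multivariate normal distribution for these provider and patient random effects".
- **The endpoint window has no named index visit.** Section 8.1.1 counts a prescription 4 weeks after the clinic visit and does not say which visit.
- **Contamination is considered on the provider's side only.** Section 5.1 justifies randomising providers by the risk that a provider exposed to an intervention applies it to control patients. It does not consider a patient who moves between providers.

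**The concern.** A patient random effect is needed only if a woman can contribute more than one primary outcome, so section 8.5 places repeat visits in the primary model. That term allows a woman's outcomes to be correlated. It does not represent what she learned at an earlier visit under another arm.

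The Arm 2 and Arm 3 content is an animation about PrEP and a personal risk message. A woman who has seen both and next sees an Arm 1 provider still carries that knowledge. If her second visit is labelled Arm 1, the control group contains women who have received the patient intervention, and the estimated effect of Arms 2 and 3 against control shrinks. Recruiting more patients would not cure this, because it is bias rather than noise.

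The score of 4-10 that admits a visit to the primary population is self-reported. At a return visit it is answered by a woman who may already have seen what a medium or high score triggers. Entry to the analysis is then measured after exposure and could differ by earlier arm. The protocol gives no basis for the direction or size of that selection.

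**Working it through.** **Step 1. Can a woman exposed in Arm 2 or 3 enter as an Arm 1 record?**
- She has an eligible visit with an Arm 2 or 3 provider, scores 4-10 and sees the content (section 4).
- She returns within the three years of enrolment (section 8.3). The annual exam is an eligible visit type (section 5.1), and section 5.3 does not exclude earlier participants.
- The second provider is in Arm 1. Arm is programmed from the provider (sections 4 and 5.1), and no section fixes her first arm.
- She scores 4-10 again, and the visit enters the model with a patient random effect (section 8.5).

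Nothing in the protocol breaks this chain. Exposure does require a score of 4-10 at the earlier visit, because low scorers receive only the HIV test message (section 4).

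**Step 2. The plan's own figures (section 8.3).**
- Patients per arm: 1,170 / 3 = 390.
- Design effect: 1 + (28 - 1) x 0.01 = 1.27, as stated. (The 28 is given as a yearly figure, but 1,170 / 42 = 27.9 is the three-year total.)
- Effective patients per arm: 390 / 1.27 = 307.
- Power for 6% against 15%, using power = Φ[(d - 1.96 x SE0) / SE1]. SE0 uses the pooled proportion and SE1 the separate proportions; two-sided alpha of 0.05 is assumed because none is stated. With d = 0.09, SE0 = 0.02474 and SE1 = 0.02447: (0.09 - 0.04849) / 0.02447 = 1.70, so power is 95.5%.

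The stated 80% is not reproduced. That is a separate matter; here 95.5% serves only as the undiluted reference.

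**Step 3. Dilution.** Let g = (share of Arm 1 records from women already exposed in Arm 2 or 3) x (fraction of the effect carried over). The protocol gives neither factor, so g is an assumption. For example, g = 10% could be 20% of Arm 1 records with half the effect carried over. Arm 1 uptake becomes 6% + g x 9 points, and the intervention arm stays at 15%. Records per arm are held fixed.

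| g | Arm 1 uptake | Difference (points) | Power, 307 effective per arm |
|---|---|---|---|
| 0 | 6.00% | 9.00 | 95.5% |
| 5% | 6.45% | 8.55 | 93.0% |
| 10% | 6.90% | 8.10 | 89.7% |
| 20% | 7.80% | 7.20 | 80.3% |

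The planned analysis in non-Latinx Black women has less room. With 585 / 3 = 195 per arm and 195 / 1.27 = 153.5 effective, the same formula gives 73.2% at g = 0, 62.4% at 10% and 51.0% at 20%.

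**Step 4. Arm 2 against Arm 3.** Section 4 states that the patient content of these two arms is the same, so a woman moving between them carries no differing patient material. Their contrast can change only if an earlier Arm 3 alert or PrEP offer has a lasting effect. That would raise Arm 2 when she moves there, and so would partly offset the dilution of Arm 2 against Arm 1.

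**The case against.** **Attribution at a return visit is not written out.** The reference to intention to treat, the mention of an initial visit, and the statement that each patient is assigned to an arm could all mean that a woman keeps her first arm. If so, what remains is a record-selection rule of the kind often left to a statistical analysis plan. This stands in part: provider-based attribution at every visit is the natural reading of sections 4, 5.1 and 8.5, but it is a reading. It does not dispose of the point. Section 8.5 itself raises the change of provider and prescribes a handling that does not address carry-over. Under the alternative reading, two analysts could build different primary datasets from the same text.

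**The loss may be small.** This stands. Few switchers would cost little: 93.0% power at g = 5%, and the protocol's claimed 80% is still met until about one fifth of the effect is lost. A reader might multiply high assumed rates of return, provider change and carry-over and reach a much lower power. The protocol supports none of those rates. A high share of returns within a fixed 390 records per arm would also mean far fewer than the 390 women that section 8.3 counts.

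**Direction is not certain for every woman.** Those already prescribed PrEP, or who declined it earlier, may respond differently at a return visit. This also stands.

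**Two further inferences are marginal.** A reader might infer that one prescription is counted in two arms. A prescription written at the first visit precedes the second and falls outside its window. Only one written after the second visit, and within 4 weeks of the first, could count for both. A reader might also infer that a departing provider's patients pass to a replacement in another arm. Section 8.4 says only: "New providers who join a practice after another provider has left will undergo randomization". It does not say that patients transfer.

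**Conclusion.** The concern holds in a limited form. Section 8.5 keeps return visits in the primary model and meets a change of provider with a term that models correlation but not carry-over. On the natural reading, women exposed in Arm 2 or 3 can enter as Arm 1 records, and their eligibility at that visit is assessed after exposure.

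The expected bias is towards no difference for Arms 2 and 3 against Arm 1, provided carry-over is positive. It would be tempting to say that every arm contrast is diluted. The protocol does not support that, because Arms 2 and 3 share the same patient content and the effect on their contrast is uncertain.

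The size cannot be derived from the protocol. The power range of 95.5% to 80.3% for g from 0 to 20% is illustrative and rests on the assumed g, two-sided alpha of 0.05, the stated design effect and fixed record counts. This should be fixed as a cheap improvement; it does not undermine the trial as a whole. Confidence is moderate.

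**What to change.** In section 8.5, define the primary analysis as one record per woman:
- **Record:** her first eligible visit with a score of 4-10.
- **Arm:** that of the enrolled provider scheduled for that visit, kept whatever happens later.
- **Outcome:** a PrEP prescription within 4 weeks counted from that visit, with section 8.1.1 worded to match.

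Use later visits only in a sensitivity or exploratory analysis that records the arm or arms to which the woman was exposed before. The patient random effect is then not needed in the primary model; the provider random effect stays.

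The cost is a few sentences and one filter on data already being pulled from the EHR. The downside is that repeat records leave the primary analysis. The planned sample size does not suffer on paper, since section 8.3 counts 1,170 patients rather than visits. The rule should be settled before outcome data are analysed by arm.

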## 8.3 Sample Size Estimate and Power.

A priori sample size calculation for the three-arm RCT was based on the expected annual patient volume across six clinics of approximately 7,800. We make the conservative assumption that 5-10% of these will score medium/high-risk on the Gyn HIV Risk Tool based on our preliminary studies, yielding 390 patients annually, with a total of 1,170 over three years of enrollment. Our estimate is conservative as we found that close to 70% of patients in one of our clinics scored medium/high, but these were adolescents and young adult women who have the highest prevalence of STIs and risk behaviors. These 1,170 patients will be seen by an expected 42 providers, where providers will be randomized to receive the potential intervention along with their patients. Given that patients using the same provider are not likely to be strongly related to each other in their choices for PrEP uptake (our co-primary outcome), we assume a low intra-provider correlation (IPC) of 0.01, with on average 28 patients per provider per year, yielding a design effect of  $1 + (28 - 1) * IPC = 1.27$ . Given these assumptions, if we estimate PrEP uptake at 6% (prelim data), we will be able to detect a difference of 9% (from 6 to 15%) between arms with 80% power. We will examine the intervention effect within specific race/ethnicity groups. We will include race and ethnicity in our minimizing of differences between arms at randomization, so we can assume that race and ethnicity will be similarly distributed across arms. Assuming we have approximately 50% non-Latinx Black patient participants (as we do for the general patient population), we expect to enroll 585 non-Latinx Black patients, allowing for 80% power to detect a difference of 6% in PrEP uptake in the standard of care arm to 15% in the intervention arms, assuming the same design effect of 1.27.

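### The primary model picks its covariates from differences seen between arms and has no term for clinic or race/ethnicity, the factors used to balance the allocation

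*Protocol*

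**What the plan says.** On allocation, Protocol section 8.4 randomises 42 providers, 14 per arm, by Pocock and Simon minimisation and adds: "The study arms will be balanced over the different clinics with equal sampling rates". Section 8.3 names a second factor: "We will include race and ethnicity in our minimizing of differences between arms at randomization". It then assumes that race and ethnicity will be similarly distributed across arms.

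On analysis, section 8.5 first examines whether the arms are alike "by comparing patient and provider level demographics with descriptive statistics". For the primary logistic mixed model "we will specify a random provider effect", and a random patient effect is added for patients who return. The only rule for fixed covariates is "We will adjust these comparisons for any demographic differences" observed between arms. Secondary outcomes follow the same idea: "We will consider adjustment for factors that are imbalanced between arms in these analyses". Race/ethnicity otherwise appears as a separate look at the data: "We will examine the primary outcome stratified by race/ethnicity". No section says that a balancing factor enters the primary model regardless of what the baseline comparison shows.

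**The concern.** There are two problems, and both come from wording that the protocol fixes itself.

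1. **The model does not follow the design.** When allocation is balanced on a factor that predicts the outcome, the arm contrast no longer carries that factor's variation. A model without the factor still counts that variation in the standard error, so the test rejects too rarely under the null and loses power under the alternative. The rule in 8.5 also works against the design: the better the minimisation succeeds, the less likely a balanced factor is to be adjusted for.

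2. **The model is chosen after looking.** No covariate and no threshold for a difference is named. With 14 providers per arm, some differences will appear by chance. In a logistic model the odds ratio changes its meaning with the covariates included, so the primary effect measure is not fixed in advance.

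**Working it through.** **The plan's own figures.** Section 8.3 gives 1 + (28 − 1) × 0.01 = 1.27, which reproduces. Effective size per arm is 390 / 1.27 = 307.1. The usual two-proportion formula (two-sided 5%, which is an assumption because 8.3 states no alpha) then gives 95.5% power for 6% v 15%, not the stated 80%. That gap is a separate matter. It matters here only because the trial is nearer 80% power at 6% v 12.5% (79.5% by the same formula), so the effect of adjustment is shown at both contrasts.

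**Which factors does the rule bring in?** Clinic: none of the wording covers it. Patient race: take the 50% non-Latinx Black share from 8.3, 14 × 28 = 392 patients per arm, and an assumed cut-off of 0.1 on the standardised difference.
- Chance alone: the standard error of the standardised difference is √(2/392) = 0.0714. Then 0.1/0.0714 = 1.40, and the two-sided tail is 16%.
- If providers' shares vary with SD 0.15 (assumed): the variance of the difference in shares is 2 × (0.0225/14 + 0.2275/392) = 0.00437, SD 0.066. A standardised 0.1 is 0.05 in share, 0.05/0.066 = 0.76, and the tail is 45%.

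Simulation agrees, at 15–17% and 43–48%. Race was not minimised in these figures. So race may or may not enter, depending on the draw.

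**Why the unadjusted test is conservative.** Assume 6% uptake in all arms, correlation 0.01 and a between-clinic SD of 0.4 on the logit scale (assumed). Per-provider variances of the observed proportion:
- sampling: 0.0564/28 = 0.00201
- provider: 0.01 × 0.0564 = 0.00056
- clinic: 0.0564² × 0.16 = 0.00051

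With arms balanced within clinic, the unadjusted standard error is too large by √(1 + 0.00051/0.00258) = 1.094. The nominal 1.96 acts as 2.145, which is a rejection rate of 3.2% instead of 5%. Simulation with this clinic SD and a race odds ratio of 2 gave 2.6–3.0% without and 4.7–5.0% with clinic and race in the model.

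**Power, without v with clinic and race.** One two-arm contrast, provider-level regression, 14 providers per arm, 28 patients each, 1,500 runs, Monte Carlo error about 1 point. The two values in a cell are for provider race mix constant and varying (SD 0.15).

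| Assumed prognosis | 6% v 12.5% | 6% v 15% |
|---|---|---|
| None | 73.0→70.4; 75.9→71.0 | 92.5→90.1; 92.6→90.8 |
| Race OR 1.5, clinic SD 0.2 | 75.7→75.7; 74.6→75.2 | 92.2→91.7; 93.0→92.7 |
| Race OR 2, clinic SD 0.4 | 78.5→84.9; 75.0→84.1 | 94.3→97.0; 94.8→97.7 |

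**Near the stated correlation.** On the proportion scale the correlation is about p(1 − p)σ². Provider SD 0.3 with clinic SD 0.25 gives 0.0564 × (0.09 + 0.0625) = 0.0086 at 6% and 0.0161 at 12%. With clinic SD 0.13 it is 0.0060 and 0.0113. A simulation of all 42 providers (4,000 runs), without v with clinic:
- 6% v 12%: 67% v 70% (SD 0.25) and 70% v 70% (SD 0.13)
- 6% v 15%: 91% v 93% (SD 0.25) and 93% v 93% (SD 0.13)

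**The case against.** The strongest reply is that little harm is shown. An omitted prognostic factor makes the test conservative, so false positives are not inflated. Selection looks at baseline demographics rather than outcomes, and 8.4 masks the analysts. At the protocol's own target of 6% v 15%, power exceeds 90% with or without adjustment in every setting above. All of this stands, and it limits the weight of the point. It does not make the effect measure fixed in advance. Section 12.2 also has the team analysing outcome data every six months, and nothing says the covariates are chosen before that.

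A reader might infer three stronger things that the documents do not support.

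- *That race/ethnicity would never enter.* Providers are randomised before their patients are known, so patient race can be imbalanced and then enter under the rule.
- *That 10 or more points of power are lost.* A clinic SD of 0.5 with provider SD 0.3 does give gains of about 10 to 13 points at 6% v 12%. But those SDs imply a correlation of 0.0564 × 0.34 = 0.019 at 6% and 0.1056 × 0.34 = 0.036 at 12%, about two to four times the stated 0.01.
- *That the protocol documents large clinic differences in uptake.* The figure of close to 70% in 8.3 is the share scoring medium or high in one clinic of young patients. It describes eligibility, not uptake among the eligible. Section 2.1 reports lower PrEP use among Black than White women, which makes race a plausible predictor. It gives no strength for this population, and 8.6 says the determinants of uptake are not well studied.

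The simulations also simplify the setting: section 5.1 notes that many providers work at more than one site.

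**Conclusion.** The point holds as a fault of specification with a modest, conditional cost. Certain from the text: fixed covariates depend on observed differences with no threshold, clinic cannot enter under that wording, and race/ethnicity enters only by chance. Conditional on prognostic strength, which the protocol does not give:

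- If the factors are strongly prognostic, the null rejection rate is about 3% instead of 5%. Adjusting then gains about 6 to 9 points near the 80% power point and about 3 points at 6% v 15%.
- Near the stated correlation of 0.01, the gain is about 0 to 3 points.
- If the factors are not prognostic, adjusting costs about 2 to 5 points.

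The case for change therefore rests mainly on having a primary model that is fixed in advance and matches the allocation, and only secondarily on power. An analysis plan that kept the sentence in 8.5 would inherit the fault.

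**What to change.** Replace the adjustment sentence in 8.5 with: *The primary model includes fixed effects for the minimisation factors (clinic as used in the minimisation, and race/ethnicity), plus patient race/ethnicity, whatever the observed balance.* Apply the same to the secondary outcomes, keep the baseline table descriptive, and move imbalance-driven adjustment to a sensitivity analysis.

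Two clarifications belong with it. Clinic must mean the one assigned to the provider at minimisation, because providers work across sites. The protocol should also say whether the race/ethnicity used in minimisation is the provider's own or that of the provider's patients; if it is the same variable as patient race/ethnicity, one term is enough. In the analyses stratified by race/ethnicity, the patient race term drops out and clinic stays.

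The cost is one sentence, five indicator terms for six clinics and a few for race/ethnicity. Expected events are 390 × (0.06 + 0.15 + 0.15) ≈ 140, of which about 23 are in the control arm, so the list should stay short; age and risk level are optional. The price is the 2 to 5 points of power above if neither factor turns out to be prognostic.
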